## Summative impact evaluation

The summative impact evaluation has three research questions that will be examined during the 12-month follow-up period per participant. For evaluation purposes, the start of the intervention is operationalised as the point of randomization. The end is set as either the graduation from the programme (i.e., the point at which the delivery team and the programme participant jointly agree that the individual is no longer benefitting from the programme) or as dropping out from the programme due to, for example, imprisonment or death. Since it is unlikely that each individual will become a part of the programme immediately after being randomized into the treatment group, time from randomization to first contact by the delivery team is recorded in the process data and will be accounted for in the analysis.

The summative impact evaluation questions are as follows:

What is the difference in the number of violence against the person offences attributed to individuals receiving the focused deterrence intervention compared to those of similar individuals receiving business-as-usual support?What is the difference in the time to a violence against the person offence (in days) attributed to individuals receiving the intervention compared to those of similar individuals receiving business-as-usual support?What is the difference in the number of co-offending crimes (i.e., crimes involving two or more perpetrators) attributed to individuals receiving the intervention compared to those of similar individuals receiving business-as-usual support?

### Randomisation

Eligible individuals within each site are randomised to treatment or control conditions on a 1:1 allocation ratio. Randomisation is stratified on (i) a three-point ordinal scale of frequency of offending in the past 24 months (derived from raw counts for each location but coarsened for randomisation to low, medium and high) and (ii) whether eligible participants are 18 years old and over or under 18 years of age. Stratification helps to reduce between-group differences at baseline, helping to increase statistical power with a fixed sample size [21].

Prior offending categories (tertiles) have been established from the first cohort of eligible individuals and are site-specific (i.e., grouping into low, medium and high might differ between sites). This method was chosen because it is transferrable across jurisdictions, easily accessible to analysts, and the data-generating process is relatively consistent across areas.

Our second stratification is whether a case is an adult (18 and over) or a child (under 18 years) since all sites expect a mix of such cases (noting that the minimum age is 14 years). This is necessary because statutory services in England generally treat children and adults differently, with deterrence and support provisions varying by child/adult status.

The evaluation team undertook the initial randomisation of long-listed eligible candidates as ‘batches’. Further randomisation will be undertaken on a case-by-case basis, as per a ‘trickle trial’ [22], using a dedicated randomisation platform that will record the individual’s unique ID, the site, their tertile of offending frequency, whether they are a child (under 18) at the time of randomisation, and treatment allocation. Records of treatment allocation are accessible to the trial’s delivery team and the evaluation team for data retention (trial duration plus 10 years). Random allocation of cases will be completed using the ‘randomizr’ package [23] for R v4.0.4 [24]. The sample code is recreated and available on the Open Science Framework: https://osf.io/pvnj2/.

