### Intervention sites

This multisite trial, spanning five English cities—Coventry, Leicester, Manchester, Nottingham, and Wolverhampton—implements seven distinct interventions, all structured around the YEF Focused Deterrence framework (see Table 1). While each intervention adheres to the same foundational aims and theoretical underpinnings, adaptations have been made to accommodate variations in local contexts, resource availability, and organisational structures. For a comprehensive understanding of each intervention’s unique and common elements, detailed accounts, structured following the TiDieR (Template for Intervention Description and Replication) framework, are available on the Open Science Framework: https://osf.io/pvnj2/.

**Table 1 pone.0301023.t001:** Seven interventions across five sites and four delivery teams.

Trial number	Team	Site	Intervention name
1	Leicester, Leicestershire and Rutland Violence Reduction Network	Leicester City	The Phoenix Programme
2	Greater Manchester Combined Authority	Manchester City	Another Chance Manchester
3	Nottingham Violence Reduction Unit	Nottingham City	Another Way
4	West Midlands Police	Coventry City	CIRV Coventry high risk pathway
5	West Midlands Police	Coventry City	CIRV Coventry referral pathway
6	West Midlands Police	Wolverhampton City	CIRV Wolverhampton high risk pathway
7	West Midlands Police	Wolverhampton City	CIRV Wolverhampton referral pathway

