**Fig 1 pone.0301023.g001:**
[figure not shown]
Statistical power across three effect sizes.

**Table 2 pone.0301023.t002:** Simulated data sets.

	Relative reduction			
n	0.9	0.8	0.7	0.6
**100**	0.0154	0.042	0.2275	0.3248
**200**	0.0231	0.091	0.4958	0.6393
**300**	0.029	0.1349	0.6803	0.8371
**400**	0.0354	0.1859	0.8255	0.9391
**600**	0.0348	0.2745	0.954	0.993
**800**	0.0397	0.3447	0.99	0.999
**1700**	0.04	0.6461	1	1
**2500**	0.0417	0.8334	1	1

The graph illustrates the relative importance of effect size (‘relative change’) and sample size to statistical power. Using these simulations, we concluded that it is unlikely that five sufficiently powered trials would be achievable, even in the most optimistic of treatment effects. Consequently, as the site interventions are largely homogenous—designed according to the same framework and with comparable populations—an option to pool the data from all five sites as a multi-centred trial was considered. This pooling would achieve a sample size of approximately 1,700. Based on this sample size, a relative reduction of 26% would be detectable in 80% of trials. Therefore, pooling was determined to be the best trade-off in terms of value for money and feasibility to detect a plausible effect.

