In the equation, *Y* is the outcome—in this case, a count variable measuring the number of violent offences attributed to an individual in the twelve calendar months following the randomisation of an individual. The analysis approach will be based on count outcomes. We intend to use a *zero-inflated Poisson* (as reflected in our power simulations) because many individuals will likely not have further offences in the follow-up period of 12 months post-randomisation. 1[treatment] will be a binary variable where 0 = control and 1 = treatment, and the coefficient from this variable in the model will be the focal result for the project. 2[offending frequency] is one variable used for stratification in each site. We acknowledge that there is a difference between the model used in the power calculation and the analysis model presented here (S1 File). We will update the power calculations for our statistical analysis plan once we have sample data from sites to understand the likely outcome distribution (based on pre-intervention outcome data). This will be included in the analysis as n-1 dummy categories, with the reference category being the category with the largest number of observations from low, medium, or high offending frequency (note that not pre-specifying which category now will not affect the results). 3[adult] will be a binary variable for whether an individual is an adult (over 18) (= 1) or a child (under 18 years of age) (= 0). 4[site] will be site fixed effects—dummy variables for n-1 sites, again with the site with the largest number of observations overall as the reference category (anticipated to be either Coventry or Wolverhampton in the West Midlands). We include this variable because we know, *a priori*, that sites will differ in their eligibility criteria and selection processes. Hence, we need to account for between-site variation in our analysis. Finally, 5[year/month] will be a variable that captures the year and month since the start of the delivery period. This measure will capture seasonal variation and any esoteric shocks during delivery. This will be entered as a continuous variable, but if there are model convergence problems, we will aggregate this to year-quarter. We also acknowledge that it may be necessary to include another variable for offender sex, depending on the number of females included. If necessary, this would be a binary variable with 0 = male and 1 = female, determined by sex at birth, if possible, to determine this from available data.

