
For our analysis, we will use robust standard errors and calculate 95% confidence intervals based on those (the exact specification will be clarified in the statistical analysis plan). Standard error adjustment is sensible given that this helps in the event of model misspecification and heterogeneous treatment effects [28, 29]. The model specification will be the same for primary and secondary outcomes.

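### Eq 1 adjusts for prior offending only through site-specific tertiles with coefficients shared across sites, although raw 24-month counts are held; its linear time term also cannot do what the text asks of it

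*Protocol article*

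**What the plan says.** **Prior offending.** Randomisation is stratified on frequency of offending over the past 24 months, "derived from raw counts for each location but coarsened for randomisation to low, medium and high". On the cut-points the Randomisation section says "Prior offending categories (tertiles) have been established from the first cohort of eligible individuals and are site-specific", and adds that the grouping may differ from site to site. For the model, the Intention to treat analysis section says "This will be included in the analysis as n-1 dummy categories". Eq 1 has no interaction between site and offending group.

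**Site.** Eq 1 has indicators for the sites, and the reason given is that sites differ in eligibility and selection. Table 1 is titled "Seven interventions across five sites and four delivery teams". Coventry and Wolverhampton each hold a high risk and a referral pathway, with separate trial numbers.

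**Calendar time.** The year/month term is meant to pick up seasonality and unusual events during delivery. Of its coding the article says "This will be entered as a continuous variable, but if there are model convergence problems, we will aggregate this to year-quarter".

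**What is left open.** The exact form of the standard errors, the criteria for baseline imbalance and the updated power calculation are left to the SAP. Among the covariates, the Intention to treat analysis section leaves only offender sex open. The Analysis section, when discussing imbalance, mentions previous offending as an example of a control used to increase power.

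**The concern.** Coarsening a count into three groups loses information. Here the groups are also cut differently by site, so the same label can stand for different levels of past offending. Site indicators absorb differences in average level between sites. They do not absorb differences in how far apart the three groups lie, and they recover nothing within a group. If past offending predicts later violence, the raw count should explain outcome variation that Eq 1 leaves in the residual.

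The Analysis section and Eq 1 also do not quite agree. One speaks of previous offending as a power-raising control, while the other has it only in its stratification form.

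On calendar time, a single slope describes a steady trend and nothing else. The fallback of grouping into quarters would ease convergence if time were categorical. For a continuous term it changes little, so the intended coding is unclear.

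At stake is the width of the confidence interval. The article's own Table 2 gives power of 0.6461 for a 20% reduction at n = 1,700, so precision is worth having.

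**Working it through.** **1. The plan's own figure.** The Simulation section says "This pooling would achieve a sample size of approximately 1,700" and "Based on this sample size, a relative reduction of 26% would be detectable in 80% of trials". The significance level is not stated there. I assume two-sided 0.05, in line with "we will use robust standard errors and calculate 95% confidence intervals based on those".

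- Standard error (SE) of the log rate ratio implied by Table 2 at n = 1,700 and rate ratio 0.8: −ln(0.8) / (1.960 + 0.375) = 0.2231 / 2.335 = 0.0956, where 0.375 is the normal quantile of 0.6461.
- Detectable reduction at 80% power: 1 − exp(−2.8016 × 0.0956) = 23.5%.
- SE implied by 26%: −ln(0.74) / 2.8016 = 0.3011 / 2.8016 = 0.1075.

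The 26% is therefore not reproduced from Table 2 in this way. Linear interpolation in the table gives 20% + 10% × (0.8 − 0.6461) / (1 − 0.6461) = 24.3%. That mismatch is a separate matter. Here the two figures only bracket a plausible unadjusted SE of 0.096 to 0.107.

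**2. Assumed inputs.** The article gives no outcome mean, dispersion or correlation between prior and follow-up offending. I assumed:

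- control mean 0.5 to 1.0 offences a year and overdispersion 2 to 3;
- correlation of prior and follow-up log rates 0.3 to 0.9;
- mean prior count 4 to 10;
- rate ratio between pathways 1.5 to 2.5;
- seasonal amplitude 0.15 to 0.30 on the log rate.

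As a rough check, take control mean 0.5, overdispersion 2 and 850 per arm, with the treated mean 0.4. The unadjusted SE is √[((1/0.5 + 2) + (1/0.4 + 2)) / 850] = √(8.5/850) = 0.100, inside the bracket above.

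**3. Simulation.** 500 trials per scenario, N = 1,700, 1:1 allocation stratified by site, tertile and age group, true rate ratio 0.8, negative binomial working model with robust SEs. Detectable reduction = 1 − exp(−2.8016 × SE). Power for a 20% reduction = Φ(0.2231/SE − 1.96). Variance ratios use unrounded SEs. "All" means raw count, seven pathway indicators and month categories.

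| Scenario | SE, Eq 1 | SE, + log(1+count) | Variance ratio | SE, all | Variance ratio | Detectable reduction: Eq 1 → + count → all | Power for 20%: Eq 1 → all |
|---|---|---|---|---|---|---|---|
| Mean 0.5, correlation 0.3 | 0.0983 | 0.0978 | 0.990 | 0.0964 | 0.961 | 24.1 → 24.0 → 23.7% | 62 → 64% |
| Mean 0.5, correlation 0.6 | 0.0951 | 0.0930 | 0.957 | 0.0923 | 0.941 | 23.4 → 22.9 → 22.8% | 65 → 68% |
| Mean 0.5, correlation 0.9 | 0.0902 | 0.0830 | 0.846 | 0.0826 | 0.838 | 22.3 → 20.7 → 20.7% | 70 → 77% |
| Mean 1.0, overdispersion 3, correlation 0.6 | 0.0874 | 0.0843 | 0.930 | 0.0827 | 0.894 | 21.7 → 21.0 → 20.7% | 72 → 77% |
| Mean 0.5, correlation 0.6, pathway ratio 2.5, amplitude 0.30 | 0.0977 | 0.0952 | 0.950 | 0.0935 | 0.916 | 23.9 → 23.4 → 23.0% | 63 → 67% |
| Mean 0.5, correlation 0.6, mean prior count 10 | 0.0944 | 0.0922 | 0.954 | 0.0916 | 0.940 | 23.2 → 22.8 → 22.6% | 66 → 68% |

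**4. Each change alone, as variance relative to Eq 1.**

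- Raw count: 0.846 to 0.990, a cut of 1% to 15%.
- Month categories: 0.958 to 0.984, a cut of about 2% to 4%. Quarters were not simulated.
- Site-by-tertile interactions: 0.973 to 0.992 by robust SE, with almost no gain in the empirical spread of the estimates.
- Seven pathway indicators: 0.986 to 0.997, a cut of about 1% at most.

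With many indicators, robust SEs run slightly small, so the gains for months and pathways are at the upper end.

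**5. Cross-check.** A separate simulation used seven trials of 243, annual rates 0.25 to 0.8, gamma frailty shape 0.5 to 2, rate ratio 0.74, a Poisson model with robust SEs and 120 replicates. It compared Eq 1 without the calendar term against the same model plus log(1 + count) and pathway indicators. The empirical SD fell by about 2% to 8%, so the variance fell by 1 − 0.98² = 4% to 1 − 0.92² = 15%. This agrees with step 4.

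**The case against.** Eq 1 is a valid model. It adjusts for both stratification factors and for site. Randomisation is described as within site, and the platform's listed fields include site but not pathway, so site indicators match the allocation as described. The Analysis section shows that the authors already have previous offending in mind, and the SAP may add it. The stratifier is offending in general whereas the outcome is violence against the person, so how well the count predicts the outcome is unknown. Neither simulation used the planned zero-inflated Poisson model, and the article already expects that convergence may be a problem.

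Most of this stands, and it limits the size of the point. It does not remove it. The remark in the Analysis section concerns criteria for imbalance and does not put the count into the model. The Intention to treat analysis section sets out the covariates term by term and leaves only sex open.

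The calendar-time point is mainly one of consistency. Every participant is followed for 12 months, so season at entry largely averages out of the outcome, and the gain from recoding may be smaller than simulated.

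A reader might infer more than the article supports:

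- *That Eq 1 biases the comparison.* It does not; allocation is random and the issue is precision.
- *That the change is worth 6% to 32% more participants.* This follows if the 3% to 13% fall in reported robust SE in the second simulation is taken at face value (1/0.97² = 1.06; 1/0.87² = 1.32). The empirical SD fell by only 2% to 8%, which gives 4% to 18%, and every input is assumed.
- *That merging the pathways wastes material precision.* About 1% is not material.
- *That the trial cannot recruit more people.* The article says only that no single city would suffice within the funding period.

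**Conclusion.** The point holds as a low-cost improvement to the stated model. Eq 1 uses prior offending only as two shared dummy coefficients on site-specific groups, while the raw counts are held. Adding the raw count would reduce the variance of the treatment estimate by roughly 1% to 15%, equivalent to about 1% to 18% more participants (1/0.990 and 1/0.846). It is the only one of the changes with a potentially material gain. All changes together lower the detectable reduction by about 0.4 to 1.6 percentage points and move power for a 20% reduction from 62–72% to 64–77%. Where the truth lies in these ranges depends mostly on how well past offending predicts later violence, which the article does not report.

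The linear time term does not fit its stated purpose. That is an inconsistency to correct, with little effect on the treatment estimate. The pathway question is optional: the article's own reason for site effects could extend to the high risk and referral pathways, but the site indicators are sound as they are.

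**What to change.** Before any unblinded outcome analysis:

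1. Add log(1 + raw 24-month offence count) to Eq 1. Keep the offending-group, adult and site indicators. State this in the SAP so that the model and the remark in the Analysis section agree.
2. Enter quarter of randomisation as categories in place of the continuous year/month term, and reword the fallback to match.
3. Optionally, replace the five site indicators by seven pathway indicators.

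The cost is model wording, with no new data: one degree of freedom for the count, a few for the quarters and two for the pathways, out of about 1,700 participants. Convergence should be checked in the planned zero-inflated model on pre-intervention or blinded data, because it was not tested here. The same data would show the correlation between past and later offending, and so replace the assumed range above.

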### Outcome measures

The primary outcome for the impact evaluation is the number of violence against the person offences attributed to an individual within one year of randomisation. The secondary outcomes are:

the number of days between randomisation and a recorded violence against a person offence with a Police National Computer (PNC) disposal outcome relevant to the evaluation;when there is a co-offender, the number of recorded violence against the person offences attributed to an individual with a PNC disposal outcome relevant to the evaluation; andwhen there is a co-offender, the number of any recorded offences attributed to an individual with a PNC disposal outcome relevant to the evaluation.

For the purposes of this evaluation, PNC disposal outcomes relevant to the evaluation refer to all offences specified by the Home Office’s offence codes used in the court proceedings database as Violence Against the Person offences. Police-recorded violence against the person offences measure is the best outcome to evaluate the intervention’s effectiveness as it is a standard measure of violent behaviour [25]. Despite about half of all violent behaviour not being reported to the police, this rate decreases as the violence severity increases. Approximately 79% of violence against adults treated by a medical professional is captured, representing the most serious violent offending. However, reporting rates of violence against 10–15-year-olds are considerably lower, with less than 10% of all violence and 18% of violence resulting in medical treatment being reported [26].

These outcome offences will be tracked through an individual’s PNC record. PNC metadata will be used to identify cases and outcomes related to this measure. The primary outcome is determined from PNC records using the date of any eligible offence within the trial period. The evaluation team will create a dataset using the date of randomisation as the starting point and count the number of relevant incidents within one year of allocation. This approach was chosen to measure the primary outcome and address some of the known inconsistencies in the crime recording system and Home Office outcomes codes. Primary outcome data will be collected throughout the trial and analysed during the evaluation phase. Access to data and the secure transfer and processing of the data, as well as safe reporting of results, will be governed by data processing agreements between the research team and local police forces.

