#### Data

As part of the preparation phase, the five sites were asked to develop selection/eligibility criteria for the intervention, to identify the number of these individuals in their population, and to describe the number of police-recorded violence against the person offences attributed to them in a twelve-month period. This information allowed us to describe the distribution of outcomes (negative binomial) and to identify the anticipated number of individuals in treatment and control groups.

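### The secondary outcomes carry a PNC disposal qualifier that the primary outcome and research question 2 lack, and its definition leaves a fault on either reading

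*Protocol article*

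**What the plan says.** All of this is in the protocol article.

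- **Primary outcome (Outcome measures):** "the number of violence against the person offences attributed to an individual within one year of randomisation". Ascertainment is described as follows: "The primary outcome is determined from PNC records using the date of any eligible offence within the trial period". Neither sentence mentions a disposal.
- **Research question 2 (Summative impact evaluation):** "What is the difference in the time to a violence against the person offence (in days) attributed to individuals receiving the intervention", compared with business as usual. Again there is no disposal condition.
- **First secondary outcome (Outcome measures):** days from randomisation to "a recorded violence against a person offence with a Police National Computer (PNC) disposal outcome relevant to the evaluation".
- **Second and third secondary outcomes:** counts of offences with a co-offender, the second for violence and the third for "the number of any recorded offences attributed to an individual with a PNC disposal outcome relevant to the evaluation". Both carry the qualifier.
- **Definition of the qualifier (same section):** "PNC disposal outcomes relevant to the evaluation refer to all offences specified by the Home Office’s offence codes", with the codes being those for violence against the person. This lists offence types and names no disposal result such as a charge, caution or conviction.
- **Source:** "These outcome offences will be tracked through an individual’s PNC record".

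Multiple outcome testing applies a false-discovery-rate adjustment to the two co-offending outcomes.

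**The concern.** The primary count and the time outcome are meant to describe the same behaviour, once as a frequency and once as a delay. As written, one has a condition that the other lacks, and the explanation of that condition does not match its name.

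If a disposal is needed, the time outcome depends on how fast cases are processed as well as on when people offend. It would then answer a narrower question than research question 2 and could disagree with the primary result for administrative reasons. If a disposal is not needed, the violence-code definition removes the difference between the two co-offending outcomes. Research question 3 asks about co-offending crimes in general, and only their violent part would be measured.

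**Working it through.** No sample size, power or alpha figure in the article depends on this definition, so there is no stated figure to reproduce. The check compares the wording and then sizes the loss under stated assumptions.

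**Step 1. The definitions side by side.**

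| Item | Offence type | Disposal phrase |
|---|---|---|
| Primary count | Violence | No |
| Research question 2 | Violence | No |
| Secondary 1: days to offence | Violence | Yes |
| Secondary 2: count with co-offender | Violence | Yes |
| Secondary 3: count with co-offender | Any | Yes |
| Definition of the phrase | Violence codes | Names no disposal status |

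**Step 2. Reading A: a completed disposal is required.** A participant whose only violent offence falls late in the window and has no disposal at extraction scores 1 on the primary outcome and is event-free on the time outcome. If the first of two offences lacks a disposal and the second has one, the event time is moved later.

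**Step 3. Size under reading A.** The inputs are the 12-month window (documented), a mean offence-to-disposal lag of *m* months (assumed), and extraction *g* months after the window closes (assumed). Offences are taken as uniform over the 12 months and the lag as exponential. The share of in-window offences without a disposal at extraction is

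S(m, g) = (1/12) ∫₀¹² exp(−(12 + g − t)/m) dt = (m/12) × [exp(−g/m) − exp(−(12 + g)/m)].

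For example:

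- m = 3, g = 0: 0.25 × (1 − exp(−4)) = 0.245.
- m = 6, g = 0: 0.5 × (1 − exp(−2)) = 0.432.
- m = 6, g = 6: 0.5 × (exp(−1) − exp(−3)) = 0.159.

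| Mean lag m | g = 0 | g = 6 | g = 12 |
|---|---|---|---|
| 3 months | 24.5% | 3.3% | 0.4% |
| 6 months | 43.2% | 15.9% | 5.9% |
| 12 months | 63.2% | 38.3% | 23.3% |

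For offences in the last 3 months of follow-up the share is (m/3) × [exp(−g/m) − exp(−(3 + g)/m)]. With g = 0 this gives 63.2%, 78.7% and 88.5% for m = 3, 6 and 12. The loss is concentrated at the end of the window.

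These are shares of offences, not of participants. Someone with another, disposed offence still has an event.

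**Step 4. Reading B: only the offence code matters.** The primary and time-outcome events coincide and the loss is 0%. The phrase adds nothing to secondary outcomes 1 and 2, which already specify violence. Secondary outcome 3 becomes any offence with a co-offender, restricted to violence codes, which is secondary outcome 2. The false-discovery-rate adjustment then covers one outcome twice. If the Benjamini–Hochberg procedure is meant, two identical p-values adjust to 2p/2 = p, so it changes nothing.

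**Step 5. Both conditions together.** If the phrase means a completed disposal for an offence on the violence list, the faults in steps 2 and 4 both apply.

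**The case against.** The strongest reply is that the article defines its own term. The sentence after the list of secondary outcomes explains relevant disposal outcomes by offence codes, all outcomes come from the same PNC record, and the word eligible in the primary outcome may mean the same as relevant in the secondaries. On that view no offence is lost. This stands as a possible reading, and it is why the loss must be shown from 0% upwards. It does not remove the problem, because step 4 shows that this reading merges two secondary outcomes that the article lists and adjusts as separate.

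A second reply is that a stricter, disposal-confirmed secondary outcome beside a broader primary is a legitimate design, and that extraction timing belongs in the analysis plan or full protocol. Both points are fair. The missing extraction lag is not criticised here. But a stricter secondary would have to be stated as such, and research question 2 does not ask for one.

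A reader might also object to the planning data, described as "the number of police-recorded violence against the person offences attributed to them in a twelve-month period", or to the 79% capture figure for medically treated violence against adults, as further mismatched event definitions. The first describes inputs to the power simulation and is not an outcome definition. The second is offered in support of police-recorded violence and is not claimed for a disposal-based measure. Similarly, the loose reference to the trial period in the ascertainment sentence is settled by the next sentence, which limits the count to one year from allocation.

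**Conclusion.** The definitions conflict as stated, and a fault remains on either reading of the qualifier. If a completed disposal is required, the time outcome can contradict the primary count and loses late offences most. With assumed mean lags of 3 to 6 months, the share of in-window offences missed is 24.5% to 43.2% with extraction at month 12, 3.3% to 15.9% with six further months, and 0.4% to 5.9% with twelve. If only the offence code matters, nothing is lost from the time outcome, but the third secondary outcome duplicates the second and research question 3 is only partly answered.

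Three stronger conclusions might be inferred, and the article does not support them:

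- **That late offences definitely drop out, or that a particular share is lost.** This depends on the reading and on a lag and an extraction date that are not given.
- **That the main secondary outcome is compromised.** The article does not rank its secondary outcomes.
- **That the loss differs by arm.** Enforcement is part of the intervention, so this is conceivable, but nothing in the article says that it changes the speed or likelihood of disposal.

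The effect is confined to the secondary outcomes. The primary outcome as worded, and the sample size, are unaffected.

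**What to change.** 1. Use one violence event for the primary count and the time outcome: a violence against the person offence (Home Office codes) attributed to the participant on the PNC, dated by offence from randomisation to day 365, whatever its disposal status at extraction.
2. Delete the disposal qualifier from the time outcome, so that it matches research question 2. Reword the definition sentence as a list of eligible violence offence codes.
3. Define the second secondary outcome as the same violence event with a co-offender. Remove the violence-code restriction from the third so that it covers any offence with a co-offender, as research question 3 asks.
4. If a disposal-confirmed version is wanted, report it as a sensitivity analysis, from an extract taken at one fixed lag after each participant's day 365.

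The cost is wording in the protocol and analysis plan, plus a fixed-lag PNC extract if the sensitivity version is kept. The downside is that some counted offences may later end without a conviction, which the sensitivity version would show.
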